### Baseline measurement

At baseline, comprehensive information will be collected on participants’ sociodemographic characteristics, medical history, lifestyle factors, and anthropometric and body composition measurements. In addition, psychological and cognitive assessments will be conducted to evaluate baseline cognitive function and mental health status.

Cognitive function will be assessed using validated tools, including the Montreal Cognitive Assessment (MoCA) and the Mini-Mental State Examination (MMSE), to measure general cognitive abilities. Additionally, domain-specific cognitive functions will be evaluated using tests such as the digit span test forward/backward (DST-F/B), symbol digit modalities test (SDMT), verbal fluency test (VFT), trail-making test A version (TMT-A), and logical memory test (LMT). Sensory function will be assessed with tools like the Pure Tone Audiometry (PTA) and the Sniffin’ Sticks Odor Identification Test. For a comprehensive summary of these outcomes and assessments, please refer to Table 1. The assessments above will be conducted by trained research personnel. All personnel have undergone extensive training to ensure the reliability of the testing process.

**TABLE 1 T1:** The parameters collected at baseline.

	Parameters
**Primary outcomes**	
Cognitive function	Mini-Mental State Examination (MMSE), Montreal Cognitive Assessment (MOCA)
Domain-specific cognitive function	Digit span test forward/backward (DST-F/B), symbol digit modalities test (SDMT), verbal fluency test (VFT), trail making test A version (TMT-A), logical memory test (LMT)
sensory function	Pure Tone Audiometry (PTA), Sniffin’ Sticks Odor Identification Test
**Secondary outcomes**	
Brain activation	Structural, and resting state functional magnetic resonance imaging (fMRI) data will be acquired using 3.0 Tesla scanner

At least five participants from each group will be randomly selected to undergo structural and resting-state functional magnetic resonance imaging (fMRI) using a 3.0 Tesla scanner. Structural MRI will allow for detailed assessment of brain anatomy, focusing on changes in brain volume, particularly in regions associated with cognitive function, such as the hippocampus and prefrontal cortex. Resting-state fMRI will assess brain connectivity and activation patterns without the need for task-based stimuli, making it ideal for observing intrinsic brain network activity (Dickerson and Sperling, 2008). The baseline scans will establish a reference point for each participant’s brain structure and function, while the post-intervention scans will reveal how the multi-domain intervention influences brain changes over time.

As part of the baseline characteristics assessment, participants will receive written feedback on their medical and health parameters, which include blood pressure (systolic and diastolic), blood glucose (fasting or random), body mass index (BMI), heart rate (HR), oxygen saturation (SpO_2_), and basic physical activity level (assessed through a questionnaire or pedometer). Participants will be advised to consult their doctor for appropriate medical management if any concerns are identified, such as high blood pressure, hyperglycemia, abnormal BMI, or low oxygen saturation.

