## Methods and analysis

### Objectives and study design

The TaiChi-MSS study is a randomized, controlled, single-blind trial conducted across multiple centers in Suzhou and Shanghai, in which the outcome assessors will be blinded to group assignments. Block randomization, with a fixed block size of four, will be used to allocate enrolled participants into one of four arms, ensuring balanced group allocation. A total of 22 participants will be assigned to each arm, with random allocation to the Tai Chi group (TCG), the Tai Chi combined with multisensory stimulation group (TMCSSG), the control group (CG), or the multisensory stimulation group (MSSG) according to a 1:1:1:1 allocation ratio. Outcome assessors will be masked to allocate and will not be involved in the interventions. Primary outcomes include assessing changes in cognitive function—such as attention, memory, language, visuospatial ability, and executive function—after a 24 weeks intervention period. Secondary outcomes involve evaluating sensory function through air conduction, pure tone hearing thresholds, and olfactory recognition levels, as well as analyzing the correlation between hippocampal subregion atrophy rates and volumes of auditory and olfactory regions using structural MRI.

As illustrated in Figure 1, this study will be conducted in three phases. Phase 1 is the development of the intervention, and Phase 2 comprises the screening, baseline assessment, and randomization of the participants and the execution of the multidomain intervention. Phase 3 is the approach modeling.

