### Sample size

Sample size calculation: The sample size was estimated using G*Power software, incorporating considerations for cognitive and fMRI outcomes. Adjustments were made to account for dropout rates, multiple comparisons, and desired statistical power.

For cognitive outcomes, the required sample size was calculated based on an effect size of, derived from previous studies evaluating Tai Chi interventions in older adults with MCI (Bossers et al., 2015). Similar studies report comparable effect sizes regarding improvements in cognitive function (Guo et al., 2024). To achieve 95% power at a significance level, a total of 56 participants are required. Accounting for an anticipated dropout rate of 35% (Dignan et al., 2016), the adjusted sample size is approximately 88 participants. This recruitment target considers potential challenges such as health issues or non-adherence, and measures like flexible scheduling, regular follow-ups, and participant engagement will be implemented to minimize dropout.

For the fMRI analyses, an effect size was selected based on prior research exploring brain activation and connectivity changes resulting from physical and cognitive interventions (Li et al., 2012; Vance et al., 2024). To achieve sufficient power, 36 participants are required. Considering a 20% dropout rate, the adjusted sample size is 44 participants. Participants who discontinue the fMRI assessments will remain included in the cognitive analysis to ensure comprehensive data utilization.

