### Criteria for participants’ inclusion and exclusion

The study started on 1 May 2024, and patients with MCI who lived in Shanghai and Suzhou communities were recruited. First, a geriatrician checked the following initial eligibility criteria: age 60 years or older, diagnosis of dementia reported in the patient’s medical file by the dementia diagnosis team or a medical specialist, and absence of serious health problems that could preclude safe participation (Bossers et al., 2015). Next, a trained Human Movement Sciences (HMS) research assistant tested the patients for the following additional inclusion criteria: Mini-Mental State Exam (MMSE) score of at least 19 to no more than 23 and the ability to perform the timed up-and-go test (Podsiadlo and Richardson, 2015), ADL score above 26 (Fuentes et al., 2020). Those who passed these six criteria completed a neuropsychological test and fMRI at baseline (time zero, T0) administered by an experienced and trained research assistant.

Exclusion criteria include participants with severe medical conditions (e.g., advanced cardiovascular disease, uncontrolled diabetes, cancer) or neurodegenerative disorders (e.g., Huntington’s disease, Parkinson’s disease) to ensure the study focuses on individuals with MCI. Participants with exercise limitations (e.g., recent surgery, joint issues), those unable to undergo MRI due to contraindications (e.g., pacemakers, metal implants, claustrophobia), or those with a history of excessive alcohol use (> 14 drinks/week) or smoking (> 10 cigarettes/day) will also be excluded to minimize confounding factors.

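### The imaging sample size is stated in three incompatible ways, and the five-per-group minimum does not secure the 36 evaluable participants the plan says it needs

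*Protocol article*

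**What the plan says.** The Protocol article addresses the number of people scanned in three places.

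- **Sample size:** for the fMRI analyses, "36 participants are required. Considering a 20% dropout rate, the adjusted sample size is 44 participants". The basis is described only as "For the fMRI analyses, an effect size was selected based on prior research". No effect size appears in the text at hand, and no power percentage is attached to this calculation. For the cognitive outcomes, the same section uses a different loss rate: "Accounting for an anticipated dropout rate of 35"%.
- **Criteria for participants' inclusion and exclusion:** those who met the screening criteria "completed a neuropsychological test and fMRI at baseline". People who cannot undergo MRI are excluded from the whole trial, which also points to scanning everyone.
- **Baseline measurement, text below Table 1:** "At least five participants from each group will be randomly selected to undergo structural and resting-state functional magnetic resonance imaging".

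There are four arms, filled "according to a 1:1:1:1 allocation ratio", with 22 participants in each. Brain activation measured by fMRI is a named secondary outcome in the Abstract and in Table 1.

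**The concern.** The three statements imply different numbers scanned: 44, all 88, or any number from 20 upwards. Only the sentence below Table 1 describes how a subset is to be chosen, and its minimum is less than half of the planned 44. A team could scan five per arm, comply fully with that sentence, and still fall short of the 36 in the Sample size section before anyone is lost.

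What is at stake is a secondary outcome. The Statistical analysis section relies on imaging to evaluate the intervention's effect on brain function and to explore mechanisms through correlations with cognition and sensory function. If only the minimum were scanned, the four-group comparisons would rest on about four people per arm, while the protocol would still state that the imaging sample was adequately sized.

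There is also a question of timing. Selecting participants from each group reads most naturally as happening after allocation, whereas the eligibility section places the scan at baseline among those who passed screening.

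**Working it through.** **Inputs.** Four arms, 1:1:1:1 (Objectives and study design). Imaging: 36 evaluable, 20% loss, 44 enrolled (Sample size). Minimum scanned: five per group (Baseline measurement). Alpha 0.05 two-sided (Statistical analysis). The numeric fMRI power is not stated. I take 80% to 95% as a range because 80% appears in the Statistical analysis section and 95% in the cognitive calculation.

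**Step 1: reproduce the plan's 44.** Multiplying up gives 36 × 1.20 = 43.2, rounded up to 44 = 4 × 11. Dividing by the retained fraction gives 36 / 0.80 = 45. The stated 44 matches the first and is one participant from the second, so it is reproduced. The 36 cannot be reproduced without an effect size and a power.

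**Step 2: compare the three statements.**

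| Source | Scanned | After 20% loss | Meets 36? |
|---|---|---|---|
| Sample size | 44 | 44 × 0.80 = 35.2 | in effect, yes |
| Eligibility text (all 88) | 88 | 88 × 0.80 = 70.4 | yes |
| Minimum below Table 1 | 4 × 5 = 20 | 20 × 0.80 = 16 | no |

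The minimum is 20/44 = 45% of the planned number. Its 16 completers are 16/36 = 44% of the number required.

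**Step 3: what the minimum would mean for power.** Assume a one-way F test across four groups, with 3 and N − 4 degrees of freedom and noncentrality N × f². Solve for the f that gives the assumed power at N = 36, then recompute power at smaller N.

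| Assumed power at 36 | f | N × f² at 36 / 20 / 16 | Power at 20 | Power at 16 |
|---|---|---|---|---|
| 80% | 0.585 | 12.3 / 6.8 / 5.5 | 47% | 36% |
| 90% | 0.667 | 16.0 / 8.9 / 7.1 | 59% | 46% |
| 95% | 0.735 | 19.4 / 10.8 / 8.6 | 68% | 54% |

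**Step 4: sensitivity to the assumed test.** For a group-by-time interaction with two or four time points and within-person correlation 0.5, the results are nearly the same. If 36 gives 80%, power is 46–47% at 20 and 35–36% at 16. If 36 gives 95%, it is 67–68% and 52–54%. For a two-arm t test sized at nine per arm, power with five and four per arm is 50% and 39% (80% case), or 71% and 57% (95% case). Every variant tried shows a clear shortfall at the minimum.

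**The case against.** The strongest reply is that five per group is a minimum, not a fixed size. Scanning 11 per arm satisfies both the Sample size section and the sentence below Table 1, and 44 is already the stated plan. This stands. A reader might infer that the subset is set at 20 and that the imaging outcome therefore lacks its claimed power. The documents do not support that. The shortfall arises only if the minimum, or something close to it, is what gets scanned. Nor is any percentage claimed: the wording is only "To achieve sufficient power, 36 participants are required". If the eligibility text governs, all 88 are scanned, and even a 35% loss leaves 88 × 0.65 = 57.2, well above 36.

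Three further readings are tempting and should carry no weight.

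- **44 against 45.** The difference is one participant and comes from the inflation formula used.
- **20% loss is too low.** At 35%, 44 would leave 44 × 0.65 = 28.6, below 36. But the plan sets the two rates separately for separate analyses. Cognitive follow-up runs to 9 months, while the imaging text speaks of baseline and post-intervention scans, so a lower imaging loss is not a contradiction. The documents do not say whether the 20% already covers unusable scans. What remains is a request for the reason.
- **The subset is drawn after allocation.** This is an inference from the wording, and random selection within randomised arms would not by itself bias the comparison. What remains is that the timing should be stated.

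What survives is that three statements conflict, and that the only rule for choosing a subset does not protect the number the plan requires.

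**Conclusion.** The point holds as an internal inconsistency. The Sample size, eligibility and Baseline measurement sections give different imaging numbers (36 evaluable and 44 enrolled; everyone who passed screening; a minimum of 20), and no text reconciles them. The minimum does not secure the plan's own requirement: at 20 scanned and 20% loss, 16 of the 36 needed remain.

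The size of the power loss is conditional. It assumes that only the minimum is scanned, that a four-group F test at alpha 0.05 is a fair stand-in for the planned mixed-effects model, and that 36 was sized for between 80% and 95%. On those assumptions, power is about 36% to 54% at 16 completers and 47% to 68% at 20. The article gives neither the fMRI effect size nor a numeric power, so these figures illustrate the consequence and do not measure a broken claim.

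The issue concerns a secondary outcome. It does not touch the cognitive calculation (56 evaluable, 88 enrolled).

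**What to change.** Use one imaging number throughout the protocol, by one of two routes.

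1. Raise the minimum below Table 1 to the planned 11 per arm (44 in total), and align the eligibility text so that it no longer implies a scan for everyone who passes screening.
2. Keep five per arm, withdraw the statement that the imaging sample is adequately powered, and label the fMRI outcomes exploratory, reported with interval estimates.

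Under either route, state whether the subset is drawn before or after allocation, consistently with the baseline scan in the eligibility section. If the 20% allowance is kept (route 1), also give the reason why imaging loss is taken to be lower than the 35% expected for the cohort.

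The second route costs wording only. The first adds no scans beyond the 44 that the Sample size section already plans.

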### Intervention program

A factorial experimental design with four factors 4 × 4 will be used. All participants will be randomly assigned to one of the four groups: control group (CG), Tai Chi group (TCG), multisensory stimulation group (MSSG), or Tai Chi combined with multisensory stimulation group (TCMSSG). Key characteristics will be stratified; the stratification factors considered in this study include sex, years of education, and age to ensure that the groups are balanced.

The intervention will last for 6 months, followed by assessments at baseline, 3, 6, and 9 months. These assessments will include changes in overall cognitive function, measured through attention, memory, language, visuospatial ability, and executive function. Sensory function will be evaluated using air conduction, pure tone hearing threshold, and olfactory recognition tests. Functional MRI (fMRI) will be utilized to evaluate neural network connectivity and the effectiveness of the intervention on brain function.

The intervention for the Tai Chi groups (TCG and TCMSSG) will be based on exercise recommendations for older adults from the American College of Sports Medicine (ACSM). The 6 months intervention will include three weekly sessions, each lasting 50 min. The target heart rate (THR) will be calculated using the reserve heart rate percentage method (Table 2):

**TABLE 2 T2:** Exercise intensity intervention program [Tai Chi group (TCG) and Tai Chi combined with multisensory stimulation group (TCMSSG)].

Elements of intervention	Initial stage (4 weeks)	Mid-term (10 weeks)	Late stage (10 weeks)
Intensity of exercise	45% 55% HRmax	55% 65% HRmax	65% 75% HRmax
Frequency of movement	3 times a week	3 times a week	3 times a week
Duration	40 60 min	50 70 min	50 70 min

THR=(HRmax-HRrest)×intensity⁢(45%-75%)+

HRrest⁢(Lindenberger, 2008).

Additionally, the Borg Rating of Perceived Exertion (RPE) scale will be used to monitor participants’ subjective fatigue levels during the sessions.

1. Tai Chi Group (TCG): Participants will practice four sets of eight-style Tai Chi routines focused on balance, coordination, flexibility, and strength exercises. Each session will be 50 min long, with varying exercise intensities over the course of the intervention (starting at 45% HRmax and progressing to 75% HRmax). The “Eight-Style Tai Chi” mentioned in the manuscript refers to a standardized routine. This routine is designed as an introductory Tai Chi practice, consisting of eight movements. The Eight-Style Tai Chi is entirely based on the Yang-style Tai Chi and incorporates its eight most fundamental and essential movements. The routine is concise, focuses on key principles, and is characterized by its simplicity, ease of learning, and smooth, slow execution.

2. Tai Chi Combined with Multisensory Stimulation Group (TCMSSG): In addition to the Tai Chi exercises, this group will experience multisensory stimulation through soothing music and essential oils. The music volume will be controlled, and four types of essential oils (rosemary, lemon, rose, and lavender) will be used. Each essential oil will be diffused at a separate intervention site using an aroma diffuser. At each site, the essential oil will be used in four different concentrations (3, 7, 10, and 13%), progressing from low to high concentration during the intervention to address the sense of smell’s adaptation to the scent over time. Participants will rotate through four different intervention sites (Site A, Site B, Site C, and Site D), each with a specific combination of Tai Chi and sensory stimulation (e.g., Tai Chi 1 + A music + rosemary oil diffused in 3, 7, 10, and 13% concentrations). Adjustments to the concentrations will be made during the practice to ensure optimal effectiveness.

3. Control Group (CG): Participants in the control group will not undergo any exercise intervention. They will be asked to maintain their regular daily activities, which will be monitored using the International Physical Activity Questionnaire Short Form (IPAQ-SF) every 4 weeks. It will be ensured that their physical activity does not exceed 600 METs-min/week during the intervention period (Park et al., 2023).

4. Multisensory Stimulation Group (MSSG): Participants in the MSSG will receive auditory and olfactory stimulation identical to the TCMSSG but without the Tai Chi exercises. The stimulation sessions will last for 50 min each, and participants will be asked to record their emotional responses to the stimuli after each session.

### Intervention and follow-up

The study comprises a 6 months intervention period, followed by a 3 months extended follow-up phase (see Figure 2). Outcome measures will be assessed at the outset of the study and at 3 months intervals thereafter. Additionally, a 3 months follow-up period will be conducted to ascertain the sustainability and efficacy of the implemented intervention module. During this phase, respondents will not be required to attend any sessions with the researchers.

**FIGURE 2 F2:**
[figure not shown]
Trial protocol.

### Modeling methods to reduce the risk of MCI

The third phase will be based on the analysis of the first and second phases for the prevention or reversal of the MCI multi-domain intervention module. A feasibility study and implementation will be carried out in Shanghai communities. Important strategies from Phase I and Phase II will be integrated into one module to reverse MCI in the future by establishing treatment rooms for motor combined with sensory stimulation. The model will include elements and strategies for a multi-domain intervention and is primarily used by stakeholders involved in elderly care, including policymakers, public health strategists, and health and local volunteers. These applications will provide standardized protocols and easy-to-use intervention guidelines to support the prevention and management of older adults with MCI.

### Statistical analysis

Statistical Package for Social Sciences (SPSS) software (version 23.0) will be used for statistical analysis. An alpha level of (0.05) will be considered for all statistical tests. Two-sided *P*-values of (0.05) and (80%) power indicate statistical significance (Schulz et al., 2010). A mixed effect model will analyze the results and be employed for statistical analysis of the variance of the pretest (baseline score) and posttest (3, 6, 9 months) in the four groups. All mental, cognitive, sensory, and physical outcome measures will be used for statistical analysis. Discovery Rate (FDR) correction will be used for *post hoc* analysis.

Given the variety of cognitive and fMRI outcome measures, we will apply the False FDR to control for multiple comparisons (Genovese et al., 2002). Bonferroni correction will be used only if necessary for specific hypotheses with fewer comparisons, but FDR will be the primary approach (Alspach, 1996). An intention-to-treat (ITT) approach will be employed to handle missing data (Gupta, 2011; Little, 2024). Multiple imputations will be applied for missing cognitive data. Participants with incomplete or poor-quality fMRI data, such as those affected by motion artifacts, will be excluded from the fMRI analysis but kept in the cognitive analysis. Specific handling of missing data will depend on the outcome type.

Functional MRI (fMRI) will be utilized to evaluate neural network connectivity and the effectiveness of the intervention on brain function. Pearson correlation analysis will be conducted to assess the relationship between hippocampal subregion atrophy and the volumes of auditory and olfactory regions using structural MRI data. Similarly, Pearson or Spearman correlation coefficients will be calculated, depending on the distribution of the data, to explore the associations between fMRI-derived connectivity metrics and cognitive and sensory outcomes. These analyses aim to uncover potential neural mechanisms underlying the effects of the interventions. A sensitivity analysis will be performed by varying hypothetical dropout rates and effect sizes to assess their impact on the statistical power and required sample size (Little, 2024).

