**Methods and analysis:**

The TaiChi-MSS (Tai Chi and Multisensory Stimulation for Cognitive Function) study is a multi-center, randomized controlled trial (RCT) conducted in Suzhou and Shanghai, enrolling 88 participants aged 60 years or older with MCI. Participants will be randomly assigned to one of four groups: Tai Chi, multisensory stimulation, Tai Chi combined with multisensory stimulation or control. The intervention will last 6 months, with follow-up assessments at 3, 6, and 9 months. Primary outcomes include cognitive and sensory assessments, assessed using the Montreal Cognitive Assessment (MoCA), Mini-Mental State Examination (MMSE), domain-specific cognitive tests, Pure Tone Audiometry (PTA), and Sniffin’ Sticks Odor Identification Test. Secondary outcomes involve brain activation, measured through functional Magnetic Resonance Imaging (fMRI) scans. fMRI will be used to assess brain structure and connectivity changes, focusing on neuroplasticity. Data will be analyzed using mixed-effects models. The False Discovery Rate (FDR) will be the correction method for multiple comparisons to control for the expected proportion of false positives.

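### The mixed model takes the baseline score as one of the analysed repeated scores, with no covariate or stated common-baseline constraint; in its usual form this gives a valid but less precise change-score contrast at month 6

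*Protocol article*

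**What the plan says.** The abstract says only "Data will be analyzed using mixed-effects models". The Statistical analysis section adds what is modelled: "statistical analysis of the variance of the pretest (baseline score) and posttest (3, 6, 9 months) in the four groups". On a plain reading, the baseline score is one of four repeated levels of the outcome. The article names no baseline covariate, does not say whether baseline means are free or common across arms, and does not say which model term is the treatment contrast.

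Under Objectives and study design, "Primary outcomes include assessing changes in cognitive function" after 24 weeks of intervention. Under Baseline measurement, "Cognitive function will be assessed using validated tools, including the Montreal Cognitive Assessment (MoCA) and the Mini-Mental State Examination (MMSE" and the domain tests are collected at baseline. The description of Phase 2 lists baseline assessment before randomization. Stratification, under Intervention program, is by sex, years of education and age, not by a baseline cognitive score.

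On power, the article gives two figures. The Sample size section has "To achieve 95% power at a significance level, a total of 56 participants are required". The Statistical analysis section has "Two-sided *P*-values of (0.05) and (80%) power indicate statistical significance".

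**The concern.** A baseline score taken before randomization can differ between arms only by chance. A model that gives each arm its own baseline mean ignores this. It subtracts the whole of any chance baseline difference from the later difference, although only the fraction rho of it is expected to persist. This adds noise to the contrast. In a trial with a large chance imbalance it also moves the estimate in a predictable direction.

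The arms are small: 22 randomized, and 14 each if the planned 56 are evaluable. The score that would recover the precision is already collected, so the loss is avoidable.

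**Working it through.** **Inputs from the article.** Four arms of 22, total 88; 56 required; 35% dropout; visits at baseline, 3, 6 and 9 months; two-sided alpha 0.05; MMSE entry range 19 to 23.

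**Assumed.** The baseline-to-follow-up correlation rho, shown from 0.3 to 0.9, and equal variances at baseline and follow-up.

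**The plan's own figure.** 56/(1 - 0.35) = 86.2, so 87, and the next multiple of four is 88. This agrees with the target. The 56 cannot be checked, because the effect size does not appear in the text: "the required sample size was calculated based on an effect size of, derived from previous studies". Evaluable participants per arm: 56/4 = 14.

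**Which contrast the usual model gives.** A random-intercept model with unconstrained group-by-time means was fitted to complete simulated data (four groups, four visits). The month-6 interaction contrast and the difference in mean change were both 0.00502. The identity is exact only with complete data.

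**Variance.** Per participant, in units of the outcome variance:

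- change from baseline: 2(1 - rho)
- adjusted for baseline, or with baseline means constrained equal (asymptotically the same): 1 - rho²
- ratio: (1 - rho²)/[2(1 - rho)] = (1 + rho)/2, so the cut is (1 - rho)/2

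| rho | change | adjusted | ratio | cut | N giving the precision of 56 change scores |
|---|---|---|---|---|---|
| 0.3 | 1.40 | 0.91 | 0.65 | 35% | 37 |
| 0.5 | 1.00 | 0.75 | 0.75 | 25% | 42 |
| 0.7 | 0.60 | 0.51 | 0.85 | 15% | 48 |
| 0.8 | 0.40 | 0.36 | 0.90 | 10% | 51 |
| 0.9 | 0.20 | 0.19 | 0.95 | 5% | 54 |

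A simulation of 20,000 two-arm trials with 14 per arm gave ratios of 0.78 at rho 0.5 and 0.88 at rho 0.7. These are slightly above theory because the slope has to be estimated.

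**Power at 14 per arm.** The effect is set so that the pairwise change-score contrast has the starting power (52 error degrees of freedom). It is then multiplied by the square root of 2/(1 + rho), with one degree of freedom fewer.

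| Starting power | rho 0.3 | rho 0.5 | rho 0.7 | rho 0.8 |
|---|---|---|---|---|
| 80% | 93.5% | 89.9% | 85.9% | 83.9% |
| 95% | 99.4% | 98.6% | 97.4% | 96.7% |

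The four-arm F test is similar: 94.5%, 90.7%, 86.5% and 84.3% from 80%, and 99.5%, 98.8%, 97.6% and 96.8% from 95%.

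**Chance imbalance.** The standard error of a two-arm baseline difference is the square root of 2/14 = 0.38 SD, ignoring any balance gained from stratification. At rho 0.5, a difference of that size shifts the change-score contrast by (1 - 0.5) × 0.38 = 0.19 SD, against the arm that starts higher. In the simulation, the error moved by -0.49 (rho 0.5) and -0.31 (rho 0.7) per unit of imbalance, against about 0 after adjustment. The mean error over all simulated trials was about 0 for both methods.

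**MMSE.** The entry range narrows the baseline spread, so equal variances do not hold. With an assumed source mean of 23 and SD of 3, and source correlations of 0.5, 0.7 and 0.8, the ratio is 0.957, 0.977 and 0.984. The cut is about 2 to 4%.

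**The case against.** The strongest objection is that the article does not fix the model described here. A constrained longitudinal analysis also keeps baseline in the response vector, so the quoted words fit a recommended method as well. Constraints and contrasts are often left to an analysis plan, and none is shown. This stands: the free-baseline model is the usual reading of the sentence, not a stated fact. Still, the sentence does say what is analysed, and it gives no sign of a constraint, which would be a deliberate departure from the usual model.

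Three limits on size also stand. First, the larger power gains start from the 80% in the Statistical analysis section, whereas the Sample size section ties 56 participants to 95%. From 95% the gain stays below 5 points throughout the range shown, and neither starting point can be verified. Second, MMSE, listed first in Table 1, gains little. Third, the 0.19 SD shift is conditional on an imbalance of one standard error. That variation is already counted in the variance ratio, so it is not a second harm, and stratification may make such imbalance smaller.

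A reader might infer that the planned analysis is biased or invalid, or that every treatment contrast must be a change score. The article supports neither reading. The change-score contrast is unbiased over randomization, the treatment contrast is not named, and with dropout the identity is only approximate.

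**Conclusion.** The point holds as one of efficiency and of bias conditional on chance imbalance. In its usual form the stated model uses the pre-randomization score less well than it could. The loss is 5 to 35% of the variance over rho 0.9 to 0.3 with equal variances, and much less for MMSE. The gain in power over rho 0.8 to 0.3 is about 4 to 13 points from 80%, or about 2 to 4.5 points from 95%. All of these sizes rest on an assumed correlation, and they apply only if baseline means are left free. The change is worth making because it costs almost nothing, not because the present analysis is wrong.

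**What to change.** In the Statistical analysis section, state one of two forms:

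- Keep baseline in the response vector with the 3, 6 and 9 month scores, and constrain its mean to be equal across the four arms (constrained longitudinal data analysis). This keeps participants with no post-baseline score, which matters with 35% dropout expected.
- Model the 3, 6 and 9 month scores as the response, with the baseline value of the same measure and its interaction with visit as covariates. Participants with no post-baseline score then enter only through the multiple imputation already planned.

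In either case, name the arm-by-visit contrast at month 6 as the treatment contrast, and use the same form for the sensory outcomes. The cost is one sentence and a few model degrees of freedom. No new data, visits or participants are needed.
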